**Figure 1 F1:**
[figure not shown]
Frequency and duration of follow up.

A review of safety data (growth, major morbidity) occurred after one- and two-thirds of infants completed the feeding intervention by an external Data Safety and Monitoring committee. The study was approved by the Research Ethics Committee at each participating hospital.

### Inclusion/exclusion criteria

The inclusion criteria were (1) day 1 to 4 of life; (2) <1500 g birth weight; (3) enteral feeding expected to be initiated in the first 7 days of life. The exclusion criteria were (1) infants with serious congenital or chromosomal anomalies that may contribute to poor developmental outcome; (2) severe asphyxia; (3) enrolment in any other clinical study affecting nutritional management during the feeding intervention; (4) reasonable potential that the infant would be transferred to a NICU where the study protocol could not be continued. The study feeding protocol was stopped if (1) the infant died during the intervention period; (2) a parent(s) requested withdrawal from the feeding protocol; (3) the infant had inadequate weight gain despite nutrient concentration of feedings (4) there was a requirement for thickening of feeds that would unmask the feeding assignment. In the event that an infant was withdrawn from the study feeding protocol, the family was requested to allow Research Staff to continue data collection and to complete the follow-up phase after discharge. See Figure 
2 for a review of subject disposition to date.

**Figure 2 F2:**
[figure not shown]
Subject disposition to date.

### Outcome measures

The primary outcome for this trial is the cognitive composite score on the BSID-III at 18 months CA. The BSID-III is a standardized test designed to assess the cognitive, language and motor (fine, gross) development of infants from 1 to 42 months of age
[73]. A decision was made to administer this test at each infant’s 18 month CA birth date because of the improved predictive validity at this time compared to earlier ages
[73,74].

The secondary mortality/morbidity composite comprised death and major morbidity including NEC, late onset sepsis, chronic lung disease or severe retinopathy of prematurity. Late onset sepsis was defined as a positive culture from blood, cerebrospinal fluid, catheter or suprapubic urine at >5 days after birth. A confirmed case of NEC was defined as stage 2 or 3 by the Modified Bell Staging Criteria
[75]. Infants were classified as having chronic lung disease as assessed at 36 weeks postconception by NIH criteria
[76]. Severe ROP (Stage 4 or 5) was defined according to International criteria or if laser surgery or intraocular anti-vascular injection was required
[77-79].

Weight (+/-2 g), length (+/-0.1 cm) and head circumference (+0.1 cm) were measured weekly during hospitalization and at routine post-discharge clinic visits using standardized procedures and precision equipment as previously described
[80,81]. To account for the different GA of infants, z-scores for anthropometric measurements are computed using the Fenton preterm growth charts and the World Health Organization Growth Standard after 50 weeks gestational age
[82]. Changes in weight as a consequence of the intervention will be specifically examined in relation to gains in length and head circumference as there is little evidence that weight gain alone (i.e. fat mass gain) will benefit the long-term outcome of infants.

Exploratory variables include feeding tolerance and nutrient intakes during the feeding intervention. The volume and estimated energy/nutrient density of study milk and other sources of nutrition (e.g. parenteral nutrition, mother’s own milk, vitamin supplements) were extracted prospectively from medical records by study staff during the feeding intervention. Feeding tolerance will be assessed by describing the days to full enteral feeding (150 ml/kg/d) and number of days feedings were withheld.

In addition, a health economic analysis of the use of pasteurized donor milk compared to preterm formula as a supplement to mother’s own milk is being conducted. The specific objectives of the health economic analyses are:

(i) To measure and compare the relevant health and non-health costs of neonatal care to 18 months, for VLBW infants fed donor milk or preterm formula as a supplement.

(ii) As appropriate, use measured costs in conjunction with the efficacy data from the clinical trial to estimate the cost per five-point improvement in BSID-III through use of donor milk in VLBW infants.

(iii) To use decision-analytic modeling and secondary literature sources to estimate the long-term health and non-health costs, as well as long-term quality of life outcomes and cost per quality adjusted life year, for enrolled infants, based on outcomes measured to 18 months CA.

All relevant health economic data is collected prospectively monthly from the time of study enrolment until 18 months CA.

Although some differences in resource utilization between treatment and control groups will be related to the costs of donor milk and potentially to differential neonatal therapeutic requirements if one group has improved growth or fewer adverse events such as NEC, there may be longer-term differences in costs if donor administration is associated with improvements in neurodevelopment
[83]. Unfortunately, the measurement of cost-related outcomes beyond the 18 month endpoint for the clinical trial data collection is not feasible. Instead, a decision-analytic model will be constructed to synthesize longer-term cost effectiveness estimates in a secondary analysis
[84]. In order to balance the importance of long-term cost-effectiveness with the potentially reduced validity of literature-supplemented cost estimates, results will be reported primarily in terms of measured cost-effectiveness to 18 months, and secondarily in terms of modeled cost-effectiveness through the lifetime. The former results will be of interest primarily to hospital decision makers and third-party payers, while the latter will more strictly maintain the societal perspective important to the broader clinical and policy-making audience.

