
Baseline demographic variables collected by means of parental interviews* or from medical records +.

The feeding intervention continued for 90 days including transfer to a participating level II unit or until discharge home, whichever occurred first. Other than whether infants received donor milk or preterm formula as a supplement, all other aspects of feeding were directed by the clinical team at each NICU. General feeding guidelines were agreed upon by the participating NICUs to provide a consistent approach, and to set criteria necessitating removal from the feeding protocol. These detailed guidelines are found in Table 
4. Donor milk was purchased and shipped primarily from the Mother’s Milk Bank of Ohio (>95%) with backup from Calgary Mother’s Milk Bank, both HMBANA members. Donor milk from Ohio was collected and pooled from at least three women who had delivered within the previous three months. Once nutrient fortification of donor milk commenced, a protein module (0.3 g/dl, Beneprotein, Nestle) was added to donor milk to bring the analyzed protein content (0.9 g/dl) up to the average estimated protein concentration of mother’s own milk after 30 days (1.2 g/dl)
[71,72].

**Table 4 T4:** Feeding guidelines

	**Supplement to MOM**	**Supplement to MOM**
	Pasteurized Human Donor Milk	Preterm Formula*
		Similac Special Care 20 or 24 kcal/ oz [3.0 g protein/100 kcal] [Abbott Laboratories] or
		Enfamil Premature Formula 20 or 24 kcal/oz [3.0 g protein/100 kcal] [Mead Johnson Nutritionals]
**Initiation of enteral feeding**	Day 1-7	Day 1-7
**Volume of feeding at initiation**	10-20 ml/kg/d (hold volume for 3-5 days)	10-20 ml/kg/d (hold volume for 3–5 days)
**Rate of feed advancement**	10-25 ml/kg/day	10-25 ml/kg/day
**Fortification to commence at >120 ml/kg/day using milk pumped > 7 days after parturition+**	Human milk fortifier	Not Applicable
	Enfamil Human Milk Fortifier, [Mead Johnson Nutritionals] or	
	Similac Human Milk Fortifier, [Abbott Laboratories]	
**Volume**	140-200 ml/kg/d to achieve a weight gain of > 15 g/kg/day	140-200 ml/kg/d to achieve a weight gain of > 15 g/kg/day
**Minimum protein dose to be provided once (or up to 3 days after) volume reaches >150 ml/kg/d**	3.0 g/kg/d**	3.0 g/kg/d**
**At 24 kcal/oz and weight gain < 15 g/kg/d for 3–7 days**	Concentrate feeding using a multi-nutrient modular to 26–27 kcal/oz	Modular to 26–27 kcal/oz

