### Statistical analyses

Using a 5 point difference in composite cognitive scores at 18 months CA, with 80% power (alpha level of 0.05), and an estimated standard deviation in each feeding group of 15, we estimated that we required 142 infants in each feeding arm. We assumed a 10% loss to follow-up during the feeding intervention and an additional 10% loss to follow-up after discharge, thus necessitating 176 infants to be randomized in each of the two feeding groups. As the number of infants withdrawn from the study exceeded 10%, primarily due to infant death, we overenrolled by 11 subjects to produce a final sample size of 363 subjects.

Analyses will be carried out using SAS Version 9.1 (SAS Institute, Cary, NC, USA). Descriptive statistics will be calculated for all variables of interest. Continuous measures will be summarized using means and standard deviations whereas categorical measures will be summarized using counts and percentages. The primary analysis for this intent-to-treat study will include all infants as randomized, regardless of adherence with the feeding protocol. The initial analysis will be a comparison of means (cognitive composite score) between the 2 groups at 18 months CA. A generalized linear model will carry out this comparison, controlling for length of treatment and adjusting for correlation of observations taken at the same centre. Sex, birth weight strata (<1000, 1000–1499 g), use of antenatal steroids, multiple birth, a count of key morbidities and duration of mother’s own milk-feeding are prognostic of neurodevelopmental outcome, and for this reason we will perform a secondary analysis which will include a regression model adjusted for the aforementioned characteristics
[4,6,13].

Children who cannot be tested on the BSID-III due to disability, severe delay or who perform below the threshold of the test for individual composite scores (cognitive, language motor) will be assigned a score of 49
[7]. The scores will be computed by trained individuals who have established inter rater reliability (R^2^ = 80) and who are blind to study group. Other missing data will be handled using methods of multiple imputation.

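### Feeding tolerance is to be described by raw day counts with no stated treatment of death or unequal time on the intervention; the resulting bias is modest and its direction is uncertain

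*Protocol article*

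**What the plan says.** All references are to the protocol article.

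- **Status and measures (Outcome measures).** "Exploratory variables include feeding tolerance and nutrient intakes during the feeding intervention". The two measures follow: "Feeding tolerance will be assessed by describing the days to full enteral feeding (150 ml/kg/d) and number of days feedings were withheld". The second of these, the "number of days feedings were withheld", is given without a denominator.
- **Summary (Statistical analyses).** Continuous measures are summarised by means and standard deviations.
- **Observation window (Methods/Design).** "The feeding intervention continued for 90 days including transfer to a participating level II unit or until discharge home, whichever occurred first".
- **Death and removal (Inclusion/exclusion criteria).** "The study feeding protocol was stopped if (1) the infant died during the intervention period"; the other grounds are parental request, inadequate weight gain despite concentrated feeds, and a need for thickened feeds. After withdrawal from the feeding protocol, "the family was requested to allow Research Staff to continue data collection and to complete the follow-up phase after discharge".
- **Extent (Statistical analyses).** "As the number of infants withdrawn from the study exceeded 10%, primarily due to infant death, we overenrolled by 11 subjects". The text gives no exact number and no split by arm.
- **Exposure time and missing data (Statistical analyses).** Control for length of treatment is stated only for the cognitive score. Missing data beyond the Bayley floor rule are to be multiply imputed. Death is not mentioned there.

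**The concern.** Both measures are day counts without a denominator, taken over a window whose length varies by infant and which death can close.

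Days to full feeding is a time to an event that some infants never reach. A mean and standard deviation can be calculated only for those who reach it, and who reaches it is determined after randomisation. If death before full feeding differs by arm, the two means describe differently selected infants. Multiple imputation would not solve this, because a day of full feeding after death does not exist.

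The withheld-day count always exists, but it stops growing at death or discharge. It therefore mixes how often feeds were withheld with how long the infant was observed.

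The trial itself allows that exits may depend on the supplement: death is part of a secondary composite that donor milk is hypothesised to reduce. At stake is the exploratory description of feeding tolerance, and nothing beyond it.

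**Working it through.** **The plan's own figures.** None is given for feeding tolerance. The sample size is not in dispute and reproduces: a 5-point difference, SD 15, two-sided 0.05 and 80% power give 142 per arm; 142/0.9/0.9 = 175.3, rounded up to 176; 2 × 176 + 11 = 363.

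**How many infants are involved.** Ten per cent of 363 is 36.3, so withdrawals exceeded about 36 infants. How many of them died before full feeding is not stated.

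**When full feeding can occur.** Table 4 gives initiation on day 1–7 (read here as day of life) at 10–20 ml/kg/d, a hold of 3–5 days, then advances of 10–25 ml/kg/d. With no interruption, the day on which 150 is reached = start day + hold + number of steps − 1.
- Fastest: (150 − 20)/25 = 5.2, so 6 steps; 1 + 3 + 6 − 1 = day 9.
- Slowest: (150 − 10)/10 = 14 steps; 7 + 5 + 14 − 1 = day 25.

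A death in roughly the first one to three and a half weeks can therefore come before full feeding and leave this measure undefined.

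**Withheld days, illustration 1.** All inputs are assumptions: survivors observed 45–90 days (mean 67.5) with feeds withheld on 8% of days; deaths on days 5–29 (mean 17) with feeds withheld on a share r of days.

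Mean in survivors = 67.5 × 0.08 = 5.40. Mean in infants who die = 17r. Gap between arms (B − A) = (death rate B − death rate A) × (17r − 5.40).

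| r | Mean if died | Gap, 7% vs 13% deaths | Gap, 5% vs 15% deaths |
|---|---|---|---|
| 8% | 1.36 | −0.24 | −0.40 |
| 20% | 3.40 | −0.12 | −0.20 |
| 40% | 6.80 | +0.08 | +0.14 |

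A negative gap makes the arm with more deaths look better. A simulation of 400,000 infants per arm agrees to within 0.02 day. With equal death rates of 10% the gap is 0. At r = 8% the true rate is 8.0 per 100 days in both arms, so the whole gap there is artefact. The sign changes at r = 5.40/17 = 32%.

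**Withheld days, illustration 2.** Also assumed: survivors' mean stay 65 days at 8% gives 5.2; deaths at mean day 17.5 with 24% of days withheld gives 4.2.
- 6% mortality: 0.94 × 5.2 + 0.06 × 4.2 = 5.14.
- 14% mortality: 0.86 × 5.2 + 0.14 × 4.2 = 5.06.

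The raw mean falls by 0.08 day. The rate rises from 5.14/62.15 = 8.3% to 5.06/58.35 = 8.7%, where the mean days observed are 0.94 × 65 + 0.06 × 17.5 = 62.15 and 0.86 × 65 + 0.14 × 17.5 = 58.35. The sign changes at 5.2/17.5 = 30%.

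**Scale.** With a simulated SD of about 2.5 days and about 181 infants per arm, the standard error of a difference is 2.5 × √(2/181) = 0.26 day. The 0.08-day shift is 0.3 of that. The largest gap, 0.40, is about 1.5 standard errors, but it needs about 9 deaths against 27 (5% and 15% of 181).

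**Is a rate a clean replacement?** No. Take two infants with 5.4 withheld days each, all early. Discharged at day 45, the rate is 5.4/45 = 12.0 per 100 days; observed to day 90, it is 5.4/90 = 6.0. The rate penalises early discharge, which is a good outcome.

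**The case against.** The article names two measures and says they will be described. It states no scoring rule for deaths. Nothing in it rules out censoring or a competing-risk method, and it mentions multiple imputation. A condensed article commonly leaves offsets, denominators and such methods to a full protocol or analysis plan that is not shown. The variable is exploratory, and a mortality difference would show in the secondary composite. Withdrawal from the feeding protocol need not end data collection. The withheld-day bias rests on assumed values and can go either way.

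Most of this stands. A reader might infer that infants who die are scored as the most tolerant or are dropped; the text says neither. A reader might also infer that the arm with more deaths must look better on both measures. That does not follow: the withheld-day gap changes sign at about 30%, and days to full feeding has no value, good or bad, for an infant who dies first. Nor can removal for poor weight gain be treated like death, given the provision for continued data collection.

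What the objection does not remove is that the article goes beyond silence. It fixes both the measures and, for continuous measures, the summary. A mean of days to full feeding is undefined for part of the randomised population under any reading, and imputation would have to invent values after death.

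**Conclusion.** The point holds as a minor one. For days to full feeding the problem is structural: the stated summary does not exist for infants who die before 150 ml/kg/d, and its size cannot be calculated because the text gives no deaths by arm or timing. For withheld days there may be a modest bias if deaths differ by arm: about 0.1 to 0.4 day on a mean near 5 across the assumed scenarios. It is nil when deaths are balanced in number and timing, and its direction depends on how often feeds are withheld in infants who die. Stay, death timing, mortality and withholding shares are all assumptions. The documents do not support the stronger conclusion that the feeding-tolerance result will point the wrong way. The primary outcome and sample size are unaffected.

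**What to change.** 1. Report time to full enteral feeding as cumulative incidence by arm over all randomised infants. Treat death before full feeding as a competing event, and keep infants who never reach it in the denominator.
2. State that no feeding-tolerance values are imputed after death.
3. Report withheld days with days at risk, as a rate per 100 infant-days on the intervention, beside the raw count rather than in its place. Note that early discharge also shortens the denominator.

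Feeding tolerance was already extracted prospectively or assessed weekly during the intervention, so no new collection is foreseen. The cost is slightly more analysis, and curves and rates that read less simply than mean days.

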### Statistical analyses

Using a 5 point difference in composite cognitive scores at 18 months CA, with 80% power (alpha level of 0.05), and an estimated standard deviation in each feeding group of 15, we estimated that we required 142 infants in each feeding arm. We assumed a 10% loss to follow-up during the feeding intervention and an additional 10% loss to follow-up after discharge, thus necessitating 176 infants to be randomized in each of the two feeding groups. As the number of infants withdrawn from the study exceeded 10%, primarily due to infant death, we overenrolled by 11 subjects to produce a final sample size of 363 subjects.

Analyses will be carried out using SAS Version 9.1 (SAS Institute, Cary, NC, USA). Descriptive statistics will be calculated for all variables of interest. Continuous measures will be summarized using means and standard deviations whereas categorical measures will be summarized using counts and percentages. The primary analysis for this intent-to-treat study will include all infants as randomized, regardless of adherence with the feeding protocol. The initial analysis will be a comparison of means (cognitive composite score) between the 2 groups at 18 months CA. A generalized linear model will carry out this comparison, controlling for length of treatment and adjusting for correlation of observations taken at the same centre. Sex, birth weight strata (<1000, 1000–1499 g), use of antenatal steroids, multiple birth, a count of key morbidities and duration of mother’s own milk-feeding are prognostic of neurodevelopmental outcome, and for this reason we will perform a secondary analysis which will include a regression model adjusted for the aforementioned characteristics
[4,6,13].

Children who cannot be tested on the BSID-III due to disability, severe delay or who perform below the threshold of the test for individual composite scores (cognitive, language motor) will be assigned a score of 49
[7]. The scores will be computed by trained individuals who have established inter rater reliability (R^2^ = 80) and who are blind to study group. Other missing data will be handled using methods of multiple imputation.

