## Methods/Design

This is a pragmatic multi-centre, double-blind, RCT designed to evaluate the effectiveness of pasteurized donor milk as a supplement to mother’s own milk in those infants when mother’s own milk is unavailable. The analysis will be conducted using an “intention to treat” approach. Infants randomized to the intervention group received donor milk when mother’s own milk was unavailable. Infants randomized to the control group received formula designed for preterm infants when mother’s own milk was unavailable.

Funding was received from the Canadian Institutes for Health Research (MOP#210093), SickKids Foundation and the Ministry of Health and Longterm Care of Ontario. Infants were recruited in one of four participating level III NICU in Toronto and Hamilton, Canada. A comprehensive list of parental and infant demographic variables was collected after written informed consent was secured (Table 
3). Randomization, performed within 96 hours of birth, was done centrally using a 24 hr/day web-based third party randomization service (Centre for Mother Infant and Child Research, Toronto). The study allocation was randomly assigned in a ratio of 1:1, in random blocks of 4 and 8, with stratification by centre and birth weight grouping (<1000 g and 1000–1499 g). Aside from the research dietary technicians assigned to the study and a single neonatal dietitian, all members of the research study team (including outcome assessors), clinical teams and families are blinded to study allocation.

**Table 3 T3:** Demographic variables collected during the DoMINO trial

**Infant characteristics**	**Prenatal and parental characteristics**
Gestational age at birth+	Gravity/Parity*
Birth weight, length and head circumference+	Artificial reproductive technology (type and origin of eggs, sperm)+
Size for gestational age (small [SGA], appropriate [AGA] or large for [LGA] gestational age)+	Antibiotic use prior to delivery (prior 2 weeks)+
Sex+	Use of Prenatal Steroids+
Multiple birth status+	Cesarean delivery*
5-minute Apgar score+	Mom has previously breastfed (yes/no)*
Newborn Illness severity score (SNAP-II+)	Mom intends to breastfeed (yes/no)*
	Parental education (highest degree or diploma attained)*
	Parental weight and height (self-reported)*
	Parental age*
	Number of children in current household*
	Smoking (maternal history during pregnancy)*
	First language spoken in the home*
	Socioeconomic status (single parenting; above or below poverty line)*
	Ethnicity*

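### The primary model adjusts for within-centre correlation with only four centres: if this is run with uncorrected standard errors clustered on centre, type I error would be about 18–22%, so centre should be named as a four-level fixed effect

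*Protocol article*

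**What the plan says.** The Statistical analyses section of the protocol article describes the primary comparison of mean cognitive composite scores: "A generalized linear model will carry out this comparison, controlling for length of treatment and adjusting for correlation of observations taken at the same centre". The software is SAS. The article names no GEE, sandwich or empirical standard error, random effect, fixed effect or small-sample correction.

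The Methods/Design section gives the number of centres: "Infants were recruited in one of four participating level III NICU in Toronto and Hamilton, Canada". Infants are the unit of randomization, allocated 1:1, and the same section makes centre a stratum: "in random blocks of 4 and 8, with stratification by centre and birth weight grouping". Both arms are therefore present, in near balance, in every centre.

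**The concern.** The sentence treats centre as a source of correlated observations to be modelled. The design treats it as a randomization stratum. With individual randomization inside each centre, centre differences drop out of the treatment contrast once the analysis conditions on centre, so no correlation structure is needed to protect the test.

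In a generalized linear model for a continuous score, adjusting for correlation within centre can readily be programmed as a GEE with centre as the cluster. The empirical standard error of a GEE is justified by a large number of clusters, and here there are four. It would be estimated from four centre-level contributions, with at most three degrees of freedom between them, whatever the number of infants. If it is then compared with a normal distribution, the p-value is too small and the confidence interval too narrow. This would affect the primary endpoint.

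**Working it through.** **Inputs from the protocol article (Statistical analyses; Methods/Design).** Difference 5 points, SD 15, power 80%, alpha 0.05, 142 infants per arm, four centres, 1:1 allocation within centre. **Assumed, because the article does not give them:** ICC of 0.01 or 0.05; centre sizes of 4 × 71 or 120/90/50/24.

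**1. The plan's own figure.** "Using a 5 point difference in composite cognitive scores at 18 months CA, with 80% power (alpha level of 0.05"; "an estimated standard deviation in each feeding group of 15, we estimated that we required 142 infants in each feeding arm". Two-sided normal formula: n = 2(1.96 + 0.8416)² × 15²/5² = 141.3, rounded up to 142 per arm. Two successive losses of 10%: 142/(0.9 × 0.9) = 175.3, rounded up to 176. Total: 2 × 176 + 11 = 363. All three figures reproduce, and nothing below changes them.

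**2. What an uncorrected sandwich does with four equal centres.** The four centre-level contributions behave like four values with one mean estimated from them. The expected variance estimate is then (K − 1)/K = 3/4 of the true variance, and it varies like a chi-square on 3 degrees of freedom divided by 3.
- Mean SE relative to the true SE: √0.75 × 0.921 = 0.798, where 0.921 is the mean of √(χ²₃/3).
- Rejection rate with a normal reference: P(|t₃| > 1.96 × √0.75) = P(|t₃| > 1.697) = 0.188.
- Rejection rate with t on 3 df but no K/(K − 1) correction: P(|t₃| > 3.182 × √0.75) = P(|t₃| > 2.756) = 0.070.

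**3. Simulation under no treatment effect.** 284 infants, four centres, 1:1 within centre, SD 15, 6,000 runs per row. Monte Carlo standard error at 5%: √(0.05 × 0.95/6000) = 0.3 percentage points.

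| Centre sizes | ICC | Mean sandwich SE / true SE | Sandwich, normal | Sandwich, t(3) | Sandwich × √(K/(K − 1)), t(3) | Centre fixed | Model-based (random-intercept type) |
|---|---|---|---|---|---|---|---|
| 4 × 71 | 0.05 | 0.796 | 18.4% | 6.9% | 5.0% | 5.3% | 5.2% |
| 4 × 71 | 0.01 | 0.792 | 18.8% | 7.2% | 5.1% | 5.4% | 5.6% |
| 120/90/50/24 | 0.05 | 0.742 | 22.2% | 9.1% | 6.6% | 5.2% | 5.2% |
| 120/90/50/24 | 0.01 | 0.745 | 22.1% | 8.8% | 6.4% | 5.1% | 5.0% |

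The equal-centre rows agree with step 2 (0.798, 18.8%, 7.0%). The ICC hardly matters; unequal centres make the problem worse. These runs took the ICC as known in the working correlation and model-based SE, and omitted the length-of-treatment covariate. A further simulation with that covariate and an ICC of 0 or 0.03 gave 18–22% for the uncorrected sandwich with a normal reference, 6–9% with t(3), and 4–6% for centre as a fixed effect or a model-based SE.

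**4. On the trial's scale.** The planned SE of the difference is 15 × √(2/142) = 1.78 points, so significance needs about 1.96 × 1.78 = 3.5 points. With an SE at 0.74–0.80 of that value, the bar falls on average to about 2.6–2.8 points.

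**5. If the treatment effect differs between centres** (assumed SD 3 points, mean effect zero, 4 × 71, ICC 0.05, 4,000 runs). Rejection rates are 17.8% for the uncorrected sandwich with a normal reference, 13.0% for centre fixed, 13.2% for model-based, and 4.9% for the corrected sandwich with t(3).

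**The case against.** The strongest objection is that the article never says GEE or sandwich. A random centre intercept, or a compound-symmetry model with model-based standard errors, is also an adjustment for within-centre correlation, and it holds 5.0–5.6%. A corrected sandwich with t(3) holds 5.0–6.6%. The inflation to 18–22% needs both an uncorrected sandwich and a normal reference. The estimator and the type of standard error are also details that a condensed article may leave to an analysis plan. This stands: a reader might infer that the primary test as planned will not hold its alpha, and the document does not support that.

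It does not dispose of the point. The article does not leave the handling of centre open; it fixes a correlation adjustment for a four-level stratification factor. A programmer could follow the sentence faithfully and arrive at the failing version.

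A second objection is that a fixed effect is not safer in every setting. If the treatment effect truly varies between centres, it rejects 13% of the time for the average effect, against 4.9% for the corrected sandwich. This also stands, under the assumed SD of 3 points. It concerns generalizing beyond the four centres, and a model-based SE with a random intercept only shares the same behaviour (13.2%). The uncorrected sandwich is still worse, at 17.8%.

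**Conclusion.** The point holds as a conditional one. The wording of the primary model admits an analysis that fails with four centres. If it is implemented as a GEE clustered on centre with uncorrected sandwich standard errors and a normal reference, the SE is about 20–26% too small and the type I error about 18–22%. If it is implemented as a random intercept with a model-based SE, the error rate is close to 5% under a common treatment effect, and there is no problem.

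The figures rest on assumed ICCs and centre sizes. The result is insensitive to the ICC and moderately sensitive to imbalance in centre size. The sample size of 142, 176 and 363 is unaffected. The point merits a change in wording before the primary analysis because the change is nearly free and removes the failing reading.

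**What to change.** In the Statistical analyses section, or in the analysis plan that implements it, replace the phrase on correlation within centre with: *including centre (4 levels) as a fixed effect, with model-based standard errors*. Add: *uncorrected standard errors clustered on centre will not be used*.

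The cost is three degrees of freedom out of about 280. No further data and no change to the sample size are needed. The article describes long-term follow-up as still under way and nearly all of the study team as blinded, so the wording can be settled before allocation is revealed.
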